## Methods/design

Our trial will investigate the effects of administering a single fraction of external beam radiation delivered through SBRT techniques at a dose of 25 Gy on patients with recurrent episodes of VT and in whom optimal medical therapy and previous RFA attempts have failed to provide benefit from VT burden control. We will perform matched pair analysis with dynamic cohorts. We will compare two groups of patients: One that has been treated by all the standard approaches but has not undergone VT-ART and a second group that has also received VT-ART. The entire enrolled group (by multicentric recruitment) will be stratified according to some predefined characteristics and analyzed by matched pair analysis, based on the characteristics of patients treated with VT-ART. Once a patient is enrolled to undergo VT-ART within the multicentric consortium, the search for two patients with similar feature profiles not undergoing VT-ART will be shared.

Matching factors taken into account are summarized in Table 2.

**TABLE 2 T2:** Applied matching factors.

Parameter type	Subgroup options
Etiology of cardiomyopathy*	ICM
	NICM
	ACM
Age*	
Gender*	
BMI	
LVEF*	
NYHA group*	
Ventricular arrhythmia presentations*	Sustained ventricular tachycardia incessant sustained ventricular tachycardia electrical storm
Arrhythmogenic focus anatomical intracardiac location	Based on VE exit by ECG and by the activation map of VT
Diagnostic tools used for scar definition	CT
	MR
	EAM
	ECG
TA volume*	Endocardial electroanatomic substrate mapping area/volume in all cases; epicardial mapping area/volume in the case of 3D epicardial electroanatomic substrate mapping
Heart volume	cc range
Heart-to-TA volume	cc range
Previous use of amiodaron	Y/N
Number of previous RFA attempts*	
Type of previous RFA attempts	endocardial
	epicardial
Unfeasibility to repeat RFA	Y/N
Local recurrence of TA (same area of last RFA)	Y/N
Previous percutaneous stellate ganglion blockade	Y/N

TA, target area by electroanatomical mapping; BMI, body mass index; RFA, radiofrequency ablation; LVEF, left ventricle ejecting fraction; *mandatory matching factor.

Figure 1 depicts the design of the VT-ART study.

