## Outcome measures

The primary outcome is investigating the difference in overall cardiovascular survival among the group undergoing VT-ART and the one not exposed to the innovative procedure.

The primary efficacy endpoint is a statistically significant difference in overall cardiovascular survival between the group undergoing VT-ART and the one not exposed to the innovative procedure; this will be defined in months and calculated from the time of the last procedure (represented by the last RFA for the control group and VT-ART for the innovative one, respectively).

The secondary outcome is evaluating the difference in ventricular event-free (referred to VT/VF, appropriate shock or ATP as recorded by the ICD) survival after the last procedure between the two groups (i.e., the single or last RFA in the control group and VT-ART in the innovative group). The respective endpoint is a statistically significant difference in ventricular event-free survival (in months) after the last procedure between the two groups.

An additional secondary aim is to evaluate the reduction in the number of VT episodes compared to the pre-treatment period between the two dynamic cohorts that will be investigated.

Ventricular tachycardia recurrence will be defined as evidence of monomorphic VT at ICD interrogation (either self-limiting or terminated by appropriate shock therapy or ATP). The number of VT episodes, defined as VT burden, in the 3 months before and after the procedure will then be compared.

The respective secondary endpoint will be evaluated facing 3 months before the last procedure (i.e., either RFA or VT-ART) and 3 months after.

We did set a blanking period after VT-ART before evaluate the effect on VT burden; in a recent study by Kautzner et al., the authors supported the pre-clinical theorem of myocardial apoptosis (up to 3 months post-stereotactic ablation) followed by a creation of fibrotic lesion (6–9 months post-stereotactic ablation) in the irradiated region (5). Consequently, we propose a 3-month-blanking period after the procedure.

Since a blanking period of 3 months after the procedure will be applied, the secondary endpoint will evaluate the number of VT episodes interval accounted for the last 3 months before the procedure and of the 3–6 months after it.

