### Statistical considerations and sample size for matched pair analysis

A descriptive analysis will summarize the total number and stratification of patients with RFA and VT-ART.

We will perform a comparative analysis between RFA and VT-ART in patients with structural heart disease and refractory VT. Each patient who will be treated by VT-ART will be compared with two patients in the control group treated with RFA and best standard care but without VT-ART, on the basis of the following matching factors: Etiology of cardiomiopathy (ICM, NICM, and ACM), ventricular arrhythmia presentations (sustained ventricular tachycardia; incessant sustained ventricular tachycardia; and electrical storm), diagnostic tools used for scar definition (CT, MR, EAM, and ECG), arrhythmogenic focus anatomical intracardiac location (on the basis of VE exit by ECG and by activation map of VT), TA volume (endocardial electroanatomic substrate mapping area/volume in all cases; and epicardial mapping area/volume in case of 3D epicardial electroanatomic substrate mapping), heart volume, heart-to-TA volume, rate number of previous RFA attempts, type of previous RFA attempts (endocardial and epicardial), time (in days) between the first RFA attempt and VT-ART, time (in days) between the last RFA attempt and VT-ART, previous percutaneous stellate ganglion blockade, time (in days) between the percutaneous stellate ganglion blockade and VT-ART previous use of amiodaron, NYHA group, LVEF, BMI, age, and gender.

As mentioned, applied matching factors are summarized in Table 2.

Continuous data will be expressed as mean ± standard deviation, as appropriate, for all variables collected from the entire population or specific subgroups. A comparative analysis for subsequent levels of qualitative variables through the chi-square test and quantitative variables (scores on quality of life) with the *T*-test will be performed.

Non-parametric tests will be provided where the population distribution does not have a known form (normal Gaussian).

The differences in baseline and follow-ups between the same group will be analyzed with repeated measures approach: using the Friedman test and MANOVA for continuous variables and McNemar or Cochran’s *Q*-tests for categorical ones.

The significance of the tests is fixed with *p* < 0.05.

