Once the planned number of the innovative procedure will be collected, the trial will put a 6-month observation time. If after that, 60% of the planned conventional arm patients will be collected (by all matching factors and in a 2:1 ratio), a further 3 months will be provided to reach the planned accrual. If that would have not been the case, then the patient’s enrollment will be allowed by mandatory matching factors only (only beyond that point). The detail of “mandatory matching factors” is reported in Table 2. The final analysis will be performed by the whole group and subgroup analyses, discriminating patients collected through “all matching factors” and by “mandatory-only.”

The final analysis will not be performed at all if less than a 1:1 ratio (conventional: Innovative group) of patient’s enrollment will be collected, and the study will be closed.

The final analysis will be performed specifying that the planned accrual is not met if at least a 1:1 ratio (conventional: Innovative group) enrollment will be accomplished; results will be explored and cautiously evaluated.

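### The named between-group tests (chi-square, t-test) ignore the planned 1:2 matched sets, so they are conservative and lose power

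*Protocol article*

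**What the plan says.** The Methods/design section states "We will perform matched pair analysis with dynamic cohorts" and says that the enrolled group will be "analyzed by matched pair analysis, based on the characteristics of patients treated with VT-ART". The section on statistical considerations for matched pair analysis repeats the design: "Each patient who will be treated by VT-ART will be compared with two patients in the control group treated with RFA" and best standard care.

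The same section then lists its tests:
- For comparisons: "A comparative analysis for subsequent levels of qualitative variables through the chi-square test and quantitative variables (scores on quality of life"), with chi-square for the first kind of variable and the t-test for the second.
- As a fallback: "Non-parametric tests will be provided where the population distribution does not have a known form". These tests are not specified further, and the trigger is the shape of the distribution, not the matching.
- For dependent data: "The differences in baseline and follow-ups between the same group will be analyzed with repeated measures approach", using Friedman and MANOVA for continuous variables and McNemar or Cochran's Q for categorical ones.

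The Sample size section plans 149 patients (100 controls, 49 VT-ART). If accrual on all factors falls short, "enrollment will be allowed by mandatory matching factors only (only beyond that point"). The analysis still goes ahead if the control to VT-ART ratio is at least 1:1. The primary endpoint is cardiovascular survival, and "this will be defined in months and calculated from the time of the last procedure". No test is named for it.

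**The concern.** The design creates dependence between groups: a VT-ART patient and the two controls chosen to resemble that patient share aetiology, age, LVEF, NYHA group and more. Chi-square and the ordinary t-test treat all patients as independent. The procedures on the list that could handle dependence are assigned to a different question, change over time within one group. As written, then, no named test uses the matched set, although the section is headed as a matched pair analysis.

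Two things are at stake. The first is efficiency: matching takes considerable effort here (eighteen factors in Table 2, eight of them mandatory), and an unmatched test gives back part of what it buys. The second is bias: the balance that matching gives to a pooled comparison depends on every set having the same number of controls, and the accrual rules do not guarantee that.

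**Working it through.** **Inputs.** From the article: 49 VT-ART patients, two controls each (49 × 2 = 98; the article rounds up to 100), alpha 0.05 (taken as two-sided), and a 20-point difference in VT burden response. The article gives no within-set correlation and no control response rate, so a range of correlations and a 50% versus 70% comparison are assumed.

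**The plan's own figure.** The total of 149 cannot be reproduced uniquely without a control rate. With a two-sided test of two independent proportions, a 2:1 ratio and 10% drop-out, 10% versus 30% gives 147 and 70% versus 90% gives 163; control rates of 50% to 65% give 187 to 236. None of these contains a matching term. The present point does not depend on 149.

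**Standard error, continuous outcome.** Let each outcome have variance σ² and let any two members of a set have correlation ρ. For one VT-ART patient minus the mean of two controls:
- True variance per set: σ²[1 + (1 + ρ)/2 − 2ρ] = 1.5σ²(1 − ρ).
- Variance assumed by the unpaired test: σ²[1 + 1/2] = 1.5σ².
- Ratio of standard errors, unpaired to true: 1/√(1 − ρ).

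For ρ = 0.2 this is 1/√0.8 = 1.118, about 12% too large.

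**Type I error, continuous outcome.** The unpaired test rejects when the correctly standardised difference exceeds 1.96/√(1 − ρ). At ρ = 0.2 the threshold is 1.96 × 1.118 = 2.19, and 2 × [1 − Φ(2.19)] = 2.8%. Simulation with 49 sets (20,000 runs):

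| ρ | SE ratio | Unpaired t-test | Set-difference t-test |
|---|---|---|---|
| 0 | 1.00 | 5.1% | 5.2% |
| 0.1 | 1.05 | 3.8% | 5.0% |
| 0.2 | 1.12 | 2.6% | 4.8% |
| 0.3 | 1.20 | 2.2% | 5.3% |
| 0.5 | 1.41 | 0.6% | 5.0% |

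A longer repeat (200,000 runs) gives 3.0% for the unpaired test at ρ = 0.2, so the value is best read as 2.6% to 3%.

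**Binary outcome.** Chi-square against Mantel-Haenszel stratified by set, with the correlation on a latent normal scale. Type I error is at 50% in both groups; power is for 50% versus 70%.

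| Latent correlation | Type I, chi-square | Type I, stratified | Power, chi-square | Power, stratified |
|---|---|---|---|---|
| 0 | 5.5% | 5.1% | 66% | 64% |
| 0.2 | 3.8% | 4.9% | 66% | 70% |
| 0.4 | 2.6% | 5.0% | 67% | 77% |
| 0.6 | 1.2% | 4.7% | 69% | 85% |

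**Unequal sets.** With exactly two controls per set, each matched profile has the same weight in both groups. Suppose, as an illustration, that 24 harder-to-match VT-ART patients get one control and 25 get two. There are then 24 + 50 = 74 controls. The harder profile makes up 24/49 = 49.0% of the VT-ART group but 24/74 = 32.4% of the controls. If response differs by d points between the two profiles, the pooled comparison is off by (0.490 − 0.324) × d ≈ 0.165d: about 1.7 points for d = 10 and 3.3 points for d = 20. An analysis within sets avoids this.

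**The case against.** The best defence has four parts.

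1. The article commits to matched pair analysis, so the intent is clear and only the test names lag behind. This is true, but the section does not merely stay silent: it lists tests and assigns each group of them a purpose, and those assignments conflict with the design.

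2. With fixed 1:2 sets the error is on the safe side. This stands. The unmatched tests produce fewer false positives, not more, and at zero correlation they lose nothing; the stratified test is then about one to two points less powerful.

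3. The article condenses a fuller protocol. For the survival endpoints this is decisive. A reader might infer that the primary comparison has no valid method, or that deaths will be compared by chi-square with censoring ignored. The article supports neither. No sentence applies chi-square or the t-test to survival, and a log-rank or Cox specification is commonly left to the full protocol or SAP. Nor does the five-year limit on retrospective controls show unequal follow-up: it restricts the date of the control case, while the Follow-up section sets 36 months and the same time points for retrospective data.

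4. A reader might also infer that relaxed matching goes unaddressed. The article does plan subgroup analyses separating patients matched on all factors from those matched on mandatory factors only. That is not covariate adjustment, but it is a safeguard. Adjusting every model for all ten non-mandatory Table 2 factors, several with multiple levels, would risk overfitting in 149 patients.

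**Conclusion.** The concern holds for the between-group tests that the article names: they contradict the matched design. The result is conservative tests and lost power, provided that matching induces positive correlation. At an assumed correlation of 0.2 the standard error is about 12% too large. For the binary response at latent correlation 0.4, power is 67% instead of 77%. All of these sizes rest on assumed correlations and, for power, an assumed 50% control rate. Confounding from unmatched testing arises only if set sizes vary, which the accrual rules permit but do not make certain. The finding does not extend to inflated false positives, nor to a claim that the survival endpoints lack a valid method; for those it can be said only that the article names none. This is worth correcting because the change is cheap, but it does not undermine the design.

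**What to change.** In the statistical considerations section, replace the between-group chi-square and t-test with methods that use the matched set:
- **VT burden response:** conditional logistic regression, or Mantel-Haenszel stratified by matched set.
- **Continuous outcomes, including SF36:** a model with a matched-set effect or set-clustered variance. Because SF36 is optional for RFA patients, the method should tolerate sets with missing control scores.
- **Cardiovascular survival and ventricular event-free survival:** state, or cross-refer to, a censoring-aware analysis that respects the sets, such as Cox regression with set-clustered robust variance.
- **Sets matched on mandatory factors only:** adjust for a few prespecified unmatched prognostic factors, for example unfeasibility of repeat RFA and previous amiodarone use. Keep the planned subgroup split.

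McNemar, Cochran's Q, Friedman and MANOVA can stay where they are, for change within a group.

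The cost is revised wording and slightly more analysis work. Matched-set membership must be recorded; the Table 2 factors are already collected. Set-stratified methods drop sets that carry no information, for example those in which all members have the same outcome. That is why the robust-variance form is suggested for survival.

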Other secondary objectives include identifying the benefits of VT-ART on cardiac function, as evaluated through an electrocardiogram, echocardiographic, biochemical variables, and patient’s quality of life.

In particular, we will evaluate the reduction or suspension of antiarrhythmic drug use compared to the baseline and the improvement of cardiac parameters (such as LVEF, left ventricular end-diastolic volume/diameter, ventricular strain, end-systolic volume/diameter, RVEF, and TAPSE for right ventricular function).

Analyzed biochemical variables will include heart failure biomarkers, such as NT-proB-type natriuretic peptide (NTproBNP), troponin (hs-TnI), and inflammation markers, such as polymerase chain reaction (PCR), tumor necrosis factor-alpha (TNF-alpha), and interleukin 6 (IL-6).

Improvement in the patient’s quality of life will be assessed compared to the pre-treatment period using the SF36 scale.

The patient’s QoL will be assessed before and after VT-ART using the SF36 scale (6); the post-treatment score will be compared to the pre-treatment period’s one to assess potential improvement. The post-treatment QoL evaluation will be performed at 3, 6, and 12 months after VT-ART. Once centers join the consortium, the SF36 QoL scale will be offered (although not mandatory) to all patients undergoing RFA: Before and at 6 months after conventional therapy.

Secondary outcome analyses will investigate the improvement of QoL scores after VT-ART and how QoL scores change the comparison between VT-ART and RFA.

Further secondary outcome analyses will be developed through imaging: Contrast infusion MRI and CT scan will be performed as required but not mandatory (if not contraindicated due to ICD) in the experimental arm.

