### Follow-up

Follow-up will be conducted for 36 months after treatment administration.

Patients prospectively enrolled within the consortium and treated by VT-ART will undergo ICD interrogations for up to 36 months after enrollment.

After a blanking period of 3 months, regular ICD interrogations [with intracardiac electrogram (EGM) storage of VT/VF or appropriate shock or ATP] will be prospectively collected for patients treated by VT-ART at 6, 9, 12, 18, 24, 30, and 36 months after the VT-ART procedure.

The ICD interrogation will collect the events along the last 3 months ahead of each follow-up evaluation.

Patients prospectively enrolled within the consortium and treated by RFA will undergo the same follow-up schedule if possible according to the clinical patient’s need and compliance.

Patient data retrospectively collected within the consortium and treated by either RFA or VT-ART will be retrospectively extracted at the same time points of prospective follow-up.

The final analysis will be performed only for patients with available data for the mentioned time points, either retrospectively or prospectively collected.

Quality of life will be assessed before the procedure (for prospectively enrolled patients candidate to VT-ART and RFA) and at 3, 6, and 12 months after therapy. Improvement in the patient’s quality of life will be assessed compared to the pre-treatment period using the SF36 scale.

Patient follow-up will thus, briefly, include:

•ICD interrogation (with EGM storage of VT/VF) at 6, 9, 12, 18, 24, 30, and 36 months from treatment.•A total of 12-lead ECG at 3, 6, and 12 months.•Echocardiography at 3, 6, and 12 months.•QoL assessment using the SF36 scale (7) will be performed at 3, 6, and 12 months for patients undergoing VT-ART.•QoL assessment using the SF36 scale will be performed at 6 months for patients undergoing RFA.

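### Repeated secondary outcomes are tested within group by methods that, with the available-data rule, drop any patient missing one included visit, and no longitudinal between-group estimate is planned

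*Protocol article*

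**What the plan says.** In the Protocol article, the section on statistical considerations and sample size for matched pair analysis states: "The differences in baseline and follow-ups between the same group will be analyzed with repeated measures approach". For this it names two methods, "using the Friedman test and MANOVA for continuous variables", and McNemar or Cochran's Q for categorical variables.

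Comparative analysis is handled separately in the same section. It names the chi-square test for qualitative variables and the T-test for "quantitative variables (scores on quality of life"), with non-parametric tests where normality is in doubt.

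The visits come from two other sections:
- Follow-up: "Echocardiography at 3, 6, and 12 months".
- Outcome measures, for SF36: "The post-treatment QoL evaluation will be performed at 3, 6, and 12 months after VT-ART".
- Follow-up, closing list: "QoL assessment using the SF36 scale will be performed at 6 months for patients undergoing RFA". Earlier in the same section, the running text appears to give 3, 6 and 12 months for both groups.

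The rule on incomplete patients is in Follow-up: "The final analysis will be performed only for patients with available data for the mentioned time points, either retrospectively or prospectively collected".

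Outcome measures also sets a between-group aim for quality of life, namely "how QoL scores change the comparison between VT-ART and RFA".

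**The concern.** Friedman, repeated-measures MANOVA and Cochran's Q each need a value at every occasion entered in the test. A patient with baseline, 3-month and 12-month echocardiograms but no 6-month one contributes nothing to a four-occasion test. The available-data sentence in Follow-up writes a similar restriction into the final analysis, and the article names no method that would keep such a patient.

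Missing visits can be foreseen from the document itself. Part of the data is retrospective, RFA patients follow the schedule only where possible, SF36 is optional for RFA patients, and a 10% drop-out is assumed. Deaths are also to be expected in a refractory VT population whose primary outcome is cardiovascular survival.

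The second issue is interpretation. The stated objective is to identify benefits of VT-ART on cardiac function and quality of life. Patients are treated when their arrhythmia is at its worst, so some improvement over time may occur without any effect of treatment. A within-group test cannot tell the two apart. The matched controls could, but the between-group tests named make no use of baseline values, repeated visits or the 2:1 matched sets.

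**Working it through.** The protocol gives no figure for these analyses, so there is none to reproduce. The check is how many patients a complete-case test keeps, and what that does to the estimate.

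**Inputs**
- VT-ART group: 49 (Sample size).
- Drop-out: 10% (Sample size). Whether it is overall or per visit is not stated.
- Occasions: baseline plus 3, 6 and 12 months, so k = 3 follow-up visits (Follow-up; Outcome measures).
- Per-visit missing rate m: not given. Assumed 5%, 10% or 15%, independent between visits.

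**Patients kept by a complete-case test**

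Overall, permanent drop-out: 49 × (1 − 0.10) = 44.1, about 44.

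Independent missing visits: 49 × (1 − m)^3.

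| m (assumed) | (1 − m)^3 | Kept of 49 | Share with at least one follow-up value, 1 − m^3 |
|---|---|---|---|
| 5% | 0.857 | 42.0 | 99.99% |
| 10% | 0.729 | 35.7 | 99.9% |
| 15% | 0.614 | 30.1 | 99.7% |

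The last column is the share that a mixed model could use, given a baseline value. Complete-case loss is therefore about 10% on the protocol's own figure read as overall, and 14% to 39% over the assumed per-visit range.

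**Effect on the estimate**

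A simulation compared the complete-case mean change from baseline to 12 months with the likelihood estimate that an unstructured mixed model targets. It used 49 patients, four occasions, an assumed correlation of 0.6, a true change of 0.40 SD and 1,000 runs.

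- *Missing completely at random at 5%, 10%, 15%:* both were essentially unbiased. The variance of the likelihood estimate was 0.88, 0.77 and 0.66 of the complete-case variance.
- *Missing at random, worse patients leaving, base rate 5%, 10%, 15%:* complete-case gave 0.37, 0.36 and 0.34, and the likelihood estimate 0.40, 0.40 and 0.39. Variances were then about equal (ratios 0.94, 1.03, 1.01), so the gain here is in bias, not precision.

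**Between-group side**

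The Friedman and MANOVA sentence covers change within a group. The comparative sentence names the T-test and chi-square test, read here as the usual two-sample forms because 2:1 sets are not simple pairs. Neither sentence yields a difference in change adjusted for baseline and matched set.

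For SF36, the RFA group is scheduled at 6 months under both versions of its timetable. At 3 and 12 months it is scheduled under only one of them. Six months is therefore the only time point at which a group contrast is supported on either reading.

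**The case against.** The strongest reply is that these tests are legitimate for the job they are given. A reader might infer that the plan has no between-group comparison at all, or that Friedman and MANOVA were meant to supply one. The text does not support that. The sentence is limited to within-group change, comparison goes to other tests, and MANOVA can carry a group factor and a group-by-time term. What stands is narrower: no longitudinal, baseline-adjusted comparison using the matched sets is named.

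A reader might also infer that complete-case results must look too favourable because sicker patients are lost. That is not shown. In the simulation above, the loss of worse patients made the improvement look smaller. The direction depends on the missingness mechanism.

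Nor do all the named tests lose patients to the same degree. McNemar compares two occasions and needs only that pair. The protocol does not say which visits enter each test, and the follow-up list gives no biomarker schedule. The three-visit loss therefore fits echocardiography and VT-ART SF36, but not necessarily every outcome.

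On size, the only figure in the document is 10% drop-out. Read as overall and permanent, it costs about 5 of 49 patients. Death is permanent too, so independent missing visits are an assumption that may overstate the loss.

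Finally, this is a journal article, and detail on missing data often sits in an analysis plan. That would answer silence, but here the article itself names the tests and states the available-data rule.

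**Conclusion.** The point holds for secondary repeated outcomes and does not touch the primary outcome, cardiovascular survival. Followed as written, the plan discards partly observed patients in a setting where missed visits are foreseeable. It also tests change over time without a matched between-group estimate.

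The size ranges from about 44 of 49 VT-ART patients kept (10% drop-out, overall and permanent) to 42, 36 or 30 (5%, 10% or 15% missing per visit, independent, assumed). The consequences are lost precision when visits are missing at random chance, and possible bias of unknown direction otherwise. The simulated figures rest on an assumed correlation and dropout mechanism; they illustrate the point and do not predict the trial's result.

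A mixed model is the better choice on the same data, but naming one is not sufficient. The available-data sentence could still exclude the same patients, and no model recovers SF36 scores that were never collected. A missing-at-random assumption also does not settle outcomes that do not exist after death. The change is advisable rather than essential.

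**What to change.** 1. **Continuous measures:** replace Friedman and MANOVA with a likelihood-based linear mixed model. Include group, visit, group by visit and baseline value, a patient-level random effect or unstructured within-patient covariance, and matched set as a random effect.
2. **Categorical measures:** use a mixed logistic model or weighted GEE. Unweighted GEE is not generally valid when data are missing at random.
3. **Estimate:** report the between-group difference in change at the time point common to both groups. For SF36 this is 6 months, once the two RFA timetables in Follow-up are reconciled.
4. **Available-data sentence in Follow-up:** amend it so that, for these outcomes, patients with a baseline value and at least one follow-up value are included.
5. **Deaths:** report them by group beside these results, with a sensitivity analysis for outcomes truncated by death.

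The cost is a wording change, modest extra programming and reliance on a missing-at-random assumption. No additional patients or visits are needed.
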